## **Biometrics**

In a published post-COVID cohort from Germany (Lier et al., Frontiers Neurol 2022, DOI: 10.3389/fneur.2022.988359), the median MoCA score was 27 with a interquartile range of 25 to 28. The null hypothesis is that immunoadsorption cannot reduce the score by 2 points, i.e., below the MoCA threshold. To achieve a power of 90%, according to a calculation using the G*Power Version 3.1.9.7 utility program (Faul et al., Behav Res Methods 2009), two treatment groups of 19 subjects each are required (effect size 1.0, one-sided Wilcoxon Mann-Whitney test with alpha level 0.05 and 1:1 randomization). To account for possible dropouts, the number of cases is set at 2x 20 subjects.

1. **Data management and data protection**

- Laboratory parameters will be collected. In addition, patients will complete questionnaires that allow conclusions to be drawn about their quality of life, symptom burden, cognitive abilities, and resilience in everyday life.
- Medical examinations will be carried out to assess lung function, strength, central and peripheral nervous system function, heart rhythm, and vital signs.
- Patient data and other information about blood samples and the findings of the above-mentioned examinations will be archived in a pseudonymized, password-protected database.
- The data and samples can therefore only be traced back using a key that is accessible only to the study director and the medical director of the First Medical Clinic. The data is labeled with the same key as the samples. The requirements of medical confidentiality and data protection are therefore ensured within the framework of this study.
- The data will not be passed on to third parties. The data will be stored for 10 years.
  - The data will be stored in pseudonymized form.
  - Consent can be revoked at any time in writing or verbally without giving reasons.

1. **Handling of biomaterials**

- Patient data and other information about the blood samples and the examination findings will be archived in pseudonymized form in a computerized database.
- The data and samples can therefore only be traced back using a key that is accessible only to the study director and the medical director of the First Medical Clinic. The data is labeled with the same key as the samples. The requirements of medical confidentiality and data protection are therefore maintained within the framework of this study. The database was evaluated using queries in Structured Query Language (SQL). The analyses were performed using the statistical program SPSS for Windows Version 22.

1. **Subject insurance, accident insurance**

Test subject insurance was taken out with the HDI insurance company for damages up to €500,000 per test subject and a total damage amount of €5,000,000.

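### The 90% power rests on an effect size of 1.0 that is not derived from the cited MoCA data, and on an unpaired test that does not match the crossover

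*Protocol*

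**What the plan says.** The sample size argument is in the protocol's Biometrics section and has these parts:

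- **Source of variability:** a published German post-COVID cohort in which "the median MoCA score was 27 with a interquartile range of 25 to 28". No SD is given.
- **Difference:** "The null hypothesis is that immunoadsorption cannot reduce the score by 2 points".
- **Test and effect size:** "effect size 1.0, one-sided Wilcoxon Mann-Whitney test with alpha level 0.05 and 1:1 randomization", "according to a calculation using the G*Power Version 3.1.9.7 utility program".
- **Result at 90% power:** "two treatment groups of 19 subjects each are required".
- **Enrolment:** "To account for possible dropouts, the number of cases is set at 2x 20 subjects".

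Two other places bear on it. Study design describes a crossover in which every subject is due to receive both the active and the sham cycle, and randomization fixes only the order. Section 6.1 (Primary endpoints) defines the primary comparison as values before and after active treatment and before and after sham treatment.

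**The concern.** The section moves from a cited distribution to an effect size without showing the step between them. The reader is given a 2-point difference and a 3-point interquartile range, and then an effect size of 1.0. A 2-point difference equals one SD only if the SD is 2.0, and that figure appears nowhere in the document. The usual conversion of the quoted range gives a larger SD and so a smaller effect size.

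Two further mismatches concern the design. The calculation compares two independent groups, although the trial gives both treatments to the same patients. The quoted spread is between patients at one time, whereas the endpoint is a before/after comparison. The spread that the analysis will meet is that of a within-patient difference, and it is not given.

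At stake is the one power figure in the plan. It is the stated justification for 40 patients and will be used to judge what a null result means.

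**Working it through.** **Inputs (all from Biometrics).** Quartiles 25 and 28, median 27; difference 2 points; effect size d = 1.0; one-sided α = 0.05; 1:1 allocation; 19 per group, enrolled as 20.

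**Step 1: reproduce the plan's figure.** The asymptotic-relative-efficiency method for the Mann-Whitney test with a normal parent uses N′ = 2n × 3/π, df = N′ − 2, and noncentrality d × √(N′/4), with power from the noncentral t distribution.

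- d = 1.0, n = 19: N′ = 38 × 0.9549 = 36.29; noncentrality = 1.0 × √9.07 = 3.01; power 90.4%.
- d = 1.0, n = 18: power 89.0%.

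So 19 per group is exactly right for d = 1.0. The software step is sound.

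**Step 2: from the cited data to an effect size.** For a normal distribution, the interquartile range is 1.349 SD.

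- SD = (28 − 25)/1.349 = 2.22; d = 2/2.22 = 0.90.
- Conversely, d = 1.0 needs SD 2.0, whose normal interquartile range would be 2.70.

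**Step 3: same test with d = 0.90.**

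| n per group | N′ | Noncentrality | Power |
| --- | --- | --- | --- |
| 19 | 36.29 | 2.71 | 84.4% |
| 20 | 38.20 | 2.78 | 86.0% |
| 22 | 42.02 | 2.91 | 88.9% |
| 23 | 43.93 | 2.98 | 90.1% |

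Simulation of the Mann-Whitney test at 19 per group gives 83.5%. With scores rounded and capped at the MoCA maximum of 30, it gives about 82% to 84%, depending on the direction of the shift.

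**Step 4: how firmly the quartiles fix the SD.** MoCA is scored in whole points. A rounded normal score shows quartiles 25, 27 and 28 for SDs from about 1.5 to just under 3.0.

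| SD | d = 2/SD | Power at 19 per group |
| --- | --- | --- |
| 1.5 | 1.33 | 99% |
| 2.0 | 1.00 | 90% |
| 2.22 | 0.90 | 84% |
| 3.0 | 0.67 | 63% |

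SD 2.0 is among the compatible values. With mean 26.6, the quartiles are 26.6 ± 0.6745 × 2.0 = 25.25 and 27.95, which round to 25 and 28.

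**Step 5: the contrast the crossover delivers.** The within-patient SD is not in the document, so this step rests on assumptions: SD 2.22 at each time, a common correlation ρ between a patient's scores, no carryover, and a one-sided signed-rank test with N′ = 40 × 3/π = 38.20, df = N′ − 1 and noncentrality (2/SD of the difference) × √N′.

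- *Post-treatment scores, active against sham.* SD of the difference = 2.22 × √(2(1 − ρ)). At ρ = 0 this is 3.15; noncentrality = (2/3.15) × 6.18 = 3.93; power 98.7% with 40 patients and 98.3% with 38. Any positive ρ raises it.
- *Difference between the two before/after changes.* Four scores enter, so the SD of the difference = 2 × 2.22 × √(1 − ρ). Power with 40 patients is 86% at ρ = 0 (SD 4.45), 95% at ρ = 0.3 (SD 3.72) and 98.7% at ρ = 0.5 (SD 3.15).
- In general, with 40 patients an SD of the within-patient difference of 4.0 gives d = 0.5 and power of about 92%.

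**The case against.** The strongest reply is that nothing has been miscalculated. The section states an effect size of 1.0, and 19 per group follows from it exactly. It never claims that 1.0 was obtained by dividing 2 points by an SD taken from the interquartile range; that link is the reader's. The 1.349 conversion also suits these data poorly. It assumes an unrounded symmetric distribution, whereas the quoted summary is in whole points, has a ceiling at 30, and is asymmetric (2 points below the median, 1 above). The gap between SD 2.0 and SD 2.22 is finer than whole-number quartiles can resolve. And if the between-patient spread is the wrong SD for the endpoint, 84% has no better standing than 90%.

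Most of this stands. A reader might infer that the true power is 84% and the stated 90% is false, or that the calculation contains an arithmetic error. The document supports neither: the calculation reproduces, and the cited quartiles allow SD 2.0. The reply does not rescue the 90% as a firm figure, however. The cited cohort is the only variability information offered, it does not yield 1.0, and it is compatible with power anywhere from about 63% to 99%. Nor is this a detail left for an analysis plan, since the protocol itself fixes the effect size, test and power.

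**Conclusion.** The point holds as a matter of support and fit. The effect size of 1.0 is an undocumented assumption. The usual conversion of the quoted data gives about 0.90, with power of about 84% at 19 per group and about 86% if all 20 per group complete, on the unpaired one-sided test as written. That estimate assumes a normal parent and SD 2.22, and is one point within the range of about 99% to 63% at 19 per group.

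The more basic weakness is that the figure describes two parallel groups and a spread at one time point, while the trial is a crossover with a before/after endpoint. The stated 90% is therefore not the power of the comparison the design delivers.

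A reader might also infer that the trial is too small. That does not follow. With SD 2.22, no carryover and a correlation of 0 or more, the within-patient comparison of post-treatment scores has power of about 98% or higher. If the contrast is instead the difference between two changes, power depends more on the correlation: 86% at 0, and 95% at 0.3. This is a reason to state the SD of the contrast, not to enlarge the trial.

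**What to change.** Replace the unpaired calculation in Biometrics with the power of the within-patient active-versus-sham contrast for 40 patients. Say whether the contrast uses post-treatment scores or before/after changes. State the assumed SD of the within-patient difference and its source, and show power over a range of that SD.

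If the unpaired calculation is kept, state the SD behind the effect size. Give the power as about 84% to 86% at SD 2.22 (19 to 20 per group), together with the range for SDs of 1.5 to 3.0, in place of a bare 90%.

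The cost is one restated figure and a few sentences. No additional patients are needed and trial conduct does not change.

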## **6. Target parameters**

6.1 Primary endpoints:

Effectiveness of immunoadsorption on symptom burden in patients with post-COVID syndrome measured by the values of:

- Post-COVID-19 functional status scale (PCFS)
- Chalder Fatigue Scale
- Montreal Cognitive Assessment (MOCA)
- MFI-20
- Bell Score
- Strength measurement

and comparison before and after active treatment and before and after sham treatment (before treatment cycle 1/after treatment cycle 1 and before treatment cycle 2/after treatment cycle 2).

6.2 Secondary endpoints:

- Frequency of adverse events under active and sham treatment
- Prevalence of anti-adrenergic and anti-muscarinic autoantibodies in patients with post-COVID syndrome:
  - Proportion of subjects with evidence of anti-α1-adrenoreceptor Abs
  - Proportion of subjects with evidence of anti-α2-adrenergic receptor Abs
  - Proportion of subjects with evidence of anti-β1-adrenoreceptor Abs
  - Proportion of subjects with evidence of anti-β2-adrenergic receptor Abs
  - Proportion of subjects with evidence of anti-β3-adrenoreceptor Abs
  - Proportion of subjects with evidence of anti-M1 acetylcholine receptor Abs
  - Proportion of subjects with evidence of anti-M2 acetylcholine receptor Abs
  - Proportion of subjects with evidence of anti-M3 acetylcholine receptor Abs
  - Proportion of subjects with evidence of anti-M4 acetylcholine receptor Abs
- Concentration of:
  - Anti-α1-adrenoreceptor Abs
  - Anti-α2-adrenoreceptor Abs
  - Anti-β1-adrenoreceptor Abs
  - Anti-β1 adrenoreceptor Abs
  - Anti-β1 adrenoreceptor Abs
  - Anti-M1 acetylcholine receptor Abs
  - Anti-M2 acetylcholine receptor Abs
  - Anti-M3 acetylcholine receptor Abs
  - Anti-M4 acetylcholine receptor Abs

Before and after active and sham treatment (before therapy cycle 1/after therapy cycle 1 and before therapy cycle 2/after therapy cycle 2).

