To objectively assess neurological symptoms, neurological examinations will be performed on each study participant. The initial examination will take place when participants enroll in the Gutenberg Long COVID study. To determine the possible effects of the therapy on neurological symptoms, identical examinations will also be performed after each therapy cycle.

*Vibration sensitivity*

The vibration perception threshold is measured using a tuning fork on the metatarsophalangeal joint of the big toe as an indication of a possible sensory disorder.

*Force measurement*

Muscle strength is determined, for example, by measuring the pressure exerted by the hand muscles when squeezing a rubber balloon with the dominant hand. The force applied is measured using a vigorimeter.

*Smell test*

The smell test is performed using a test battery of standardized smell sticks containing eight different smells.

*Testing pain sensitivity*

Pain sensitivity is tested using a pinprick stimulator and the sensation of pressure pain is measured using a Wagner pressure pain algometer.

- - - 1. Neurocognitive testing

Various neurocognitive functions are tested using the Montreal Cognitive Assessment (MoCA). This is a ten-minute test with various tasks that can be scored with a total of up to 30 points. It tests abilities in the areas of memory, attention, verbal abstraction, visuospatial abilities, concentration, and language comprehension.

- - - 1. Post-COVID-19 Functional Status Scale (PCFS)

The PCFS is a self-assessment tool that helps to objectively measure and compare the severity of symptoms experienced by people with post-COVID. Patients are asked to describe their condition or fill out a questionnaire. Each condition is assigned a value. The greater the severity of the symptoms described by the condition, the higher the point value on a scale of 0-4. The PCFS has been validated on cohorts of post-COVID patients and is therefore particularly suitable for assessing symptom severity.

- - - 1. Assessment of the severity of fatigue symptoms

Three different questionnaires are used to objectively assess fatigue symptoms and the resulting limitations in everyday life. These are the Chalder Fatigue Scale, the Bell Score, and the Multidimensional Fatigue Inventory (MFI-20).

- - - - 1. *Chalder Fatigue Scale*

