## **Benefit-risk assessment**

10.1 Individual benefits associated with participation in the study

- Detailed examination and objectification of the symptoms and severity of post-COVID syndrome
- Investigation of alternative causes for the symptoms and associated findings about the individual's state of health
- Advice on further treatment options in the event of a diagnosis of a disease within the scope of the study examination
- Prospect of symptom relief if the investigated immunoadsorption is effective in post-COVID

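### The protocol's only hypothesis points the wrong way: it looks for a fall in MoCA, which is deterioration, while the trial aims at improvement

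*Protocol*

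**What the plan says.** The Biometrics section starts from a published post-COVID cohort in which "the median MoCA score was 27 with a interquartile range of 25 to 28". It then states: "The null hypothesis is that immunoadsorption cannot reduce the score by 2 points, i.e., below the MoCA threshold". The sample size follows from "effect size 1.0, one-sided Wilcoxon Mann-Whitney test with alpha level 0.05 and 1:1 randomization", which gives 19 per group for 90% power, raised to 20 per group for dropouts.

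Under Medical-technical examinations, the protocol describes the MoCA: "This is a ten-minute test with various tasks that can be scored with a total of up to 30 points". It adds: "It tests abilities in the areas of memory, attention, verbal abstraction, visuospatial abilities, concentration, and language comprehension".

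Section 6.1 lists MoCA among six primary measures, under the lead-in "Effectiveness of immunoadsorption on symptom burden in patients with post-COVID syndrome measured by the values of". Section 10.1 names as a possible benefit: "Prospect of symptom relief if the investigated immunoadsorption is effective in post-COVID". Section 5 sets the examination of effects on symptom burden as the first objective.

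No other hypothesis or test direction is given for MoCA or for the other five primary measures. The amendments at the end of the protocol keep MoCA as the cognitive assessment but do not touch the hypothesis.

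**The concern.** If the null is that treatment cannot lower the score, the alternative is that it can. On a scale where points are earned for tasks solved, that alternative is cognitive worsening. The direction appears twice in the sentence, once in the verb and once in the reference to falling below a threshold, so changing one word would not repair it.

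A two-sided test would make the slip mostly cosmetic. Here the planning test is one-sided, so direction decides which results can count. A test run as the sentence reads would place its whole rejection region on the side of harm. If the tail were instead chosen after the data were seen, the one-sided error rate of 0.05 would no longer be protected.

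**Working it through.** **1. Direction of the scale.** The protocol does not say in words that a higher MoCA is better. It does say that the test covers abilities and that tasks are scored up to 30 points. More points therefore mean better performance. A 2-point fall from the cited median is 27 − 2 = 25, which is worse. The value of the threshold is not given.

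**2. The stated sample size.** Inputs from Biometrics: effect size d = 1.0, one-sided alpha 0.05, power 90%, Mann-Whitney test, 1:1. The efficiency of the Mann-Whitney test relative to the t test is taken as 3/π (normal parent; an assumption, since the protocol does not name the parent distribution).

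- Effective n per group: 19 × 3/π = 18.14
- Noncentrality: d × √(18.14/2) = 1.0 × 3.012 = 3.012
- Degrees of freedom: 2 × 18.14 − 2 = 34.3
- Power from the noncentral t distribution: 0.904. At 18 per group it is 0.890, so 19 is the smallest n that reaches 90%.

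The plan's figure is reproduced.

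**3. Reversing the sign.** The calculation uses only the absolute size of d. For an improvement of d = 1.0 tested in the improvement direction, n is again 19 per group and power 0.904.

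**4. Testing in the stated direction when the truth is improvement.** The probability of rejection in the opposite tail (normal approximation) is Φ(−d√(18.14/2) − 1.645):

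- d = 1.0: Φ(−3.012 − 1.645) = Φ(−4.657) ≈ 0.0000016
- d = 0.5: Φ(−1.506 − 1.645) = Φ(−3.151) ≈ 0.0008

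**5. Check with bounded integer scores.** Simulation with 19 per group and 4,000 runs per setting. Assumed parent: normal with mean 26.7 (the average of 25, 27 and 28), rounded and capped at 30. The SD was 2.0 or 2.22, the latter from the quoted quartiles as (28 − 25)/1.349.

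| True shift | Test for a fall rejects | Test for a rise rejects |
|---|---|---|
| +2 points (improvement) | 0% to 0.05% | 84% to 89% |
| −2 points (worsening) | 83% to 90% | 0% |

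The ceiling at 30 does not change the picture.

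**6. A two-sided 0.05 test on the same parallel-group inputs.** Power is 0.833 at 19 per group and 0.853 at 20; 24 per group are needed for 90%.

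**The case against.** The strongest reply is that this is a slip of wording with no consequence. The term one-sided appears only in the description of the sample-size input and names no tail. The aim is plain from sections 5, 6.1 and 10.1, an analysis plan may exist that sets the direction correctly, and the sample size is right either way.

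Much of this stands. The failure occurs only if the test follows the hypothesis as written. A reader might infer that the trial cannot show benefit at all, but the protocol does not support that unconditional statement. A reader might also infer that the 90% power claim fails because of the direction; step 3 shows that it does not.

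Two other stronger readings do not hold:

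- **The 2 points as a formal margin.** On that reading, power at a true 2-point effect would equal alpha, 5%. But the sentence more naturally gives a planning difference, and taken literally it places a reduction of exactly 2 points in the alternative, not on the null boundary. The wording is ambiguous; it does not establish a margin test.
- **Effect size 1.0 as the same thing as 2 points.** This needs an SD of 2.0, which the protocol does not state. The quoted quartiles suggest about 2.22 under normality, hence an effect size near 2/2.22 = 0.90. The finding on direction does not depend on this.

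What the reply does not remove is the contradiction. It sits in the only hypothesis the protocol contains, and a statement that is wrong there is not a detail left to an analysis plan. Nor can the sentence be rescued as a safety hypothesis, because MoCA is listed as a measure of effectiveness.

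**Conclusion.** The point holds and needs correction. The hypothesis contradicts the protocol's own description of MoCA and its stated aim. A one-sided test run in the stated direction would have practically no chance of showing a benefit (about 0.0000016 for a true improvement of d = 1.0, and 0% to 0.05% in the simulation of a 2-point improvement). A significant result would mean that treated patients scored worse.

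This rests on two readings: that more MoCA points mean better cognition, which the scoring description supports, and that the test follows the written hypothesis, which is the only direction given. The simulated figures also rest on the assumed score distribution.

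One-sided testing toward improvement is not shown to be an error here. Whether an unpaired calculation suits a cross-over design is a separate question.

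**What to change.** Amend the hypothesis in Biometrics to read in substance:

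- H0: the change in MoCA is no better after verum than after sham.
- H1: the change in MoCA is higher (better) after verum than after sham.

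Remove the wording about reducing the score and about the threshold, and describe the 2 points as the planning difference. Make the change before any comparison of verum with sham is seen.

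Cost: one short passage in an amendment. With the one-sided 0.05 test directed at improvement, 19 per group and power of about 0.90 stay as they are, and no extra patients or data are needed.

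A two-sided 0.05 test is an option, not a requirement, and it is not free. On the same parallel-group inputs the stated power would have to be lowered to about 0.83 at 19 per group (about 0.85 at 20), or the sample size raised to 24 per group to keep 90%.

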The Chalder Fatigue Scale is a set of 11 questions that assesses two dimensions of fatigue symptoms: physical performance and mental performance. Each question is answered using a 4-point Likert scale. It takes an average of 2-3 minutes to complete and can be repeated every 4 weeks. In the validation study, a sensitivity of 75.5% for chronic fatigue syndrome and a specificity of 74.5% were achieved.

The Chalder Fatigue Scale should be completed by each study participant as part of the evaluation examinations, before and after therapy cycle 1, before and after therapy cycle 2, and in the follow-up examination. It is completed digitally using a questionnaire on a tablet (iPad).

- - - - 1. *Bell Score*

The Bell Score is an assessment tool that can be used by both the patient and the examiner to measure the degree of limitation in daily life caused by fatigue symptoms. The limitation can be rated on a scale of 11, from 0 (bedridden) to 100 (no limitations, normal ability to perform all activities of daily living).

The Bell Score should be completed by each study participant as part of the evaluation examinations before and after therapy cycle 1, before and after therapy cycle 2, and in the follow-up examination. It is completed digitally using a questionnaire on a tablet (iPad).

- - - 1. Medical Research Council (MRC) Dyspnea Scale

In order to objectify the perceived dyspnea symptoms, make them more comparable, and be able to assess the possible effect of therapy on dyspnea symptoms, patients are asked about their symptoms using the MRC Dyspnea Scale, which uses 4 statements assigned a point value of 1-4 that describe situations in which dyspnea occurs. The subjects must then select the statement that best describes their situation.

- - - 1. Cranial MRI

All subjects are undergoing a cranial MRI at the Mainz Neuroimaging Institute as part of the Gutenberg Long COVID Study. The results will be used in the study " " to assess whether the patients' symptoms could have causes other than long COVID and whether patients with certain abnormalities respond particularly well or particularly poorly to therapy, as well as to investigate a possible correlation between the presence of autoantibodies and abnormalities in the MRI. T1, T2-TSE FLAIR, and rsfMRI will be measured on a Siemens Magnetron TRIO T3.

| Examination | Results from the Gutenberg Long Covid Study (evaluation) | Time |
| --- | --- | --- |
| Medical history interview and questionnaire | Yes | E |

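### The protocol's only stated hypothesis points the wrong way: its alternative is a 2-point fall in MoCA, which is cognitive worsening

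*Protocol*

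**What the plan says.** The Biometrics section takes its reference values from a published post-COVID cohort, in which "the median MoCA score was 27 with a interquartile range of 25 to 28". It then gives the hypothesis: "The null hypothesis is that immunoadsorption cannot reduce the score by 2 points, i.e., below the MoCA threshold". The sample size of 19 per group for 90% power follows, with these inputs in parentheses: "effect size 1.0, one-sided Wilcoxon Mann-Whitney test with alpha level 0.05 and 1:1 randomization". The total is rounded up to 2 x 20 for dropouts.

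The neurocognitive testing paragraph under Medical-technical examinations describes MoCA: "This is a ten-minute test with various tasks that can be scored with a total of up to 30 points". It adds: "It tests abilities in the areas of memory, attention, verbal abstraction, visuospatial abilities, concentration, and language comprehension".

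Section 6.1 defines the primary endpoint as effectiveness on symptom burden, measured by six instruments of which MoCA is one. Section 10.1 lists as an individual benefit: "Prospect of symptom relief if the investigated immunoadsorption is effective in post-COVID". Neither place gives a hypothesis, and the amendments at the end of the protocol do not touch the Biometrics section.

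**The concern.** MoCA points are earned by completing tasks, so more points mean better function. A null hypothesis that the treatment cannot lower the score has as its alternative that the treatment does lower it. Rejecting that null would show cognitive harm, whereas the trial is run to look for relief.

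Direction would matter less for a two-sided test, but the test used for the sample size is one-sided, and there the direction fixes the rejection region. If the sentence were carried unchanged into the analysis, a true improvement in MoCA would have practically no chance of being declared. If the direction were corrected only after results by treatment were known, the choice of tail would be open to challenge and the one-sided 0.05 error rate could no longer be relied on.

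**Working it through.** **Inputs.** From Biometrics: median MoCA 27; change of interest 2 points; effect size d = 1.0; one-sided Wilcoxon-Mann-Whitney test; alpha 0.05; 1:1 allocation; power 90%; 19 per group. From the neurocognitive testing paragraph: an ability test with a maximum of 30 points.

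**Step 1: direction as written.**
- Null: immunoadsorption does not lower MoCA by 2 points.
- Alternative: it does. 27 - 2 = 25, which the sentence itself places below the threshold. (The protocol does not give the threshold value.)
- On a scale where points are earned for ability, this is worsening.
- Replacing the verb alone does not repair the sentence. An increase ending below the threshold makes no sense, so the threshold clause must go too.

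**Step 2: reproduce the plan's figure.** For the Mann-Whitney test with a normal parent distribution, use the asymptotic relative efficiency 3/π = 0.955 and the noncentral t distribution.
- Effective n per group: 19 x 0.955 = 18.14
- Degrees of freedom: 2 x 18.14 - 2 = 34.3
- Noncentrality: 1.0 x √(18.14/2) = 3.01
- Power at one-sided 0.05: 0.904

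Nineteen is the smallest group size that reaches 0.90, so the stated number reproduces.

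**Step 3: the same test in each direction, 19 per group.**

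| True effect of immunoadsorption on MoCA | Rejects in the written direction (MoCA lower) | Rejects in the benefit direction (MoCA higher) |
| --- | --- | --- |
| Improves, d = 1.0 | 0.000002 | 0.904 |
| Improves, d = 0.5 | 0.0009 | not calculated |
| None | 0.05 | 0.05 |
| Worsens, d = 1.0 | 0.904 | 0.000002 |

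The 0.000002 is the same noncentral t calculation with noncentrality -3.01. The last row follows from the first by symmetry.

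**Step 4: simulation.** In 6,000 simulated trials with normal data and a shift of one SD towards improvement, the written direction rejected in none and the benefit direction in 0.898. Rounding scores to whole points, capping them at 30 and assuming an SD of 3/1.349 = 2.22 from the interquartile range gave 0.83 for a 2-point rise tested towards benefit. Tested in the written direction, the same rise was rejected in none. The lower 0.83 reflects mainly the larger assumed SD (2/2.22 = 0.90 instead of 1.0). The contrast between directions does not depend on normality.

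**Step 5: effect of correcting the direction.** The calculation depends on the size of d and not its sign. With d = +1.0 the answer is again 19 per group with power 0.904. Only the rejection region moves.

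**The case against.** The strongest reply is that the protocol sets no decision rule. The one-sided test stands in a parenthesis of sample-size inputs. Section 6.1 asks only for comparisons before and after each treatment, section 5 speaks of examining effects, and no place names a confirmatory test, a rejection region or a success criterion. An SAP, not shown here, may fix the tail. A reader might infer that the trial would declare success for cognitive harm and could not detect benefit. The protocol does not support that: it is true only of the hypothesis taken literally together with the test used to size the trial. This part of the reply stands.

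It is also fair that a slip is likely. The aim is plain from sections 6.1 and 10.1, the text reads as a translation, and an analyst running a benefit test backwards is a remote prospect. The very small probability in the table would arise for any well-powered one-sided test pointed the wrong way. It describes the wording, not a forecast for this trial.

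A reader might also take the sentence as a template for all six primary measures. Nothing in the protocol applies it beyond MoCA.

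The reply does not remove the error. The sentence is wrong as it stands, and its threshold clause repeats the wrong direction. A safety or non-inferiority reading does not rescue it either. That would put the fall in MoCA into the null, whereas here the fall is the alternative and a difference of effect size 1.0 is powered. An SAP that tests improvement would contradict the protocol rather than complete it.

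**Conclusion.** The point holds as a directional error in the protocol's only stated hypothesis. The alternative is a 2-point fall on a scale where a fall is worsening, contrary to the aim of the trial, and nothing else in the document corrects it. Taken literally with the test used for sizing, the chance of rejecting when MoCA truly improves by d = 1.0 is about 0.000002, against about 0.90 in the benefit direction. These figures assume 19 per group, one-sided alpha 0.05, the protocol's own effect size and a normal parent distribution.

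The sample size is unaffected. Whether the final analysis would have used the wrong tail cannot be told from the protocol, and a drafting slip is the likelier explanation. It should still be corrected, because a one-sided test needs its direction fixed before results by treatment are seen.

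**What to change.** Before unblinding, amend the Biometrics section so that:
- the null is that immunoadsorption does not increase MoCA relative to sham, and the alternative is that it does, with 2 points (effect size 1.0) as the powered difference;
- the closing clause about the MoCA threshold is deleted.

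If directional tests are planned for other primary scales, add one line giving the direction of benefit for each. The protocol shows that lower is better on PCFS, where higher values mean more severe symptoms on a scale of 0-4. It shows that higher is better on the Bell Score, which runs "from 0 (bedridden) to 100 (no limitations, normal ability to perform all activities of daily living". It does not give the scoring direction of the Chalder Fatigue Scale or MFI-20, so the sponsor should confirm both. Any SAP should carry the same statement.

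The cost is one or two sentences by amendment. Nineteen per group stays, and no extra patients or data are needed.
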